### Sample size calculation

The inclusion of 28 GPs per arm will provide a power of 80% to detect a difference of 0.8 points in SPPB score change between arms (1.2 points increase in the control group, versus 2 points in the intervention group), with 5 patients for each GP, an intra-cluster correlation coefficient of 0.15, and with a standard deviation of inter-individual variability of 1.7. Accounting for loss to follow-up, it is planned to randomize 30 GPs in each group, giving a total of 60 GPs and 300 patients (5 patients for each GP). The power of the study was calculated using the method described by Donner and Klar [40] and with the package CRTsize in the R program, version 3.3.1 (R foundation, Vienna, Austria).

### Statistical analyses

The patient characteristics at inclusion will be described according to each group (intervention and control groups). A summary table will be provided in order to ensure the homogeneity of the prognostic factor distributions according to the groups. A second summary table of clusters (GPs) will also be provided. The method and the presentation of the results will be according to the guidelines for cluster trials [41].

#### Primary outcome

All analyses of the primary outcome will be performed on the intent-to-treat population. The distribution of the primary outcome (difference in SPPB scores between inclusion and 6-month visits) will be described and presented for the two groups (graphical representation, e.g. boxplot). The primary outcome will be analyzed using a multiple linear regression model. When the conditions for application of the linear model are not respected (normality of residuals, independently distributed residuals…), a transformation (logarithmic or even Box-Cox, quantile, or z-score) of the SPPB score will be considered.

The main analysis of the primary outcome will be adjusted on the center using a mixed effect linear model with a random GP effect, and as fixed effects: an intervention effect (the control group as reference), a period effect (the inclusion as reference), and an interaction between treatment and period. This model will also be adjusted on the age at inclusion. An interaction between the SPPB at inclusion and intervention will be added to the model to test whether the treatment effect is different for patients with lower vs. higher level of SPPB score at inclusion. *P*-values and 95% confidence intervals of the fixed effects will be provided. Another analysis using the SPPB score as independent variable in a longitudinal mixed effect linear model will also be considered.

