### Outcomes and measurements (Table 3)

#### Primary outcome

The primary outcome will be the difference in SPPB scores between inclusion and 6-month visits. To allow comparison, the SPPB will be evaluated by the same GP as far as possible. The SPPB measure reflects the performance status in 3 dimensions: balance, gait, strength/endurance are evaluated by examining ability to stand with the feet together in the side-by-side, semi-tandem and tandem positions, time to walk 4 or 6 m, and time to rise from a chair and return to the seated position 5 times [39].

**Table 3 Tab3:** Schedule of outcome assessments

	Baseline	Intervention Group			Control Group	
		M 3	M 6	M 12	M 6	M 12
SPPB score	X	X	X	X	X	X
Walk test distance	X		X	X	X	X
SPPB	X	X	X	X	X	X
Physical activity	X		X	X	X	X
ADL/IADL	X		X	X	X	X
SF 12	X		X	X	X	X
Serious falls assessments	X		X	X	X	X
Hospitalization	X			X		X
Institutionalization				X		X
Weight, BMI	X	X	X	X	X	X
MNA	X					
Social score	X					
Charlson Index	X					
Medication inventory	X					

*PASE* Physical Activity Scale for the Elderly, *SF12* 12-Item Short Form Health Survey, *BMI* Body Mass Index, *MNA* Mini Nutritional Assessment, *CRP* C-Reactive Protein, *GDS* Geriatric Depression Scale, *GP* General Practitioners, *EPICES Evaluation de la précarité et des Inégalités de santé dans les centres de santé* (in French)

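### The fallback lets the primary SPPB analysis change scale after residuals are seen, by options that cannot cure dependence and mostly leave the point scale

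*Protocol article*

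**What the plan says.** The protocol article, under Outcomes and measurements, defines the endpoint as a signed change: "The primary outcome will be the difference in SPPB scores between inclusion and 6-month visits".

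Under Statistical analyses, Primary outcome, it first states: "The primary outcome will be analyzed using a multiple linear regression model". It then gives a fallback for when the model conditions are not met, naming two of them: "normality of residuals, independently distributed residuals". The fallback is that "a transformation (logarithmic or even Box-Cox, quantile, or z-score) of the SPPB score will be considered".

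The next paragraph gives the main analysis, "using a mixed effect linear model with a random GP effect", with fixed effects for intervention, period and their interaction.

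The Sample size calculation powers the trial "to detect a difference of 0.8 points in SPPB score change between arms": 1.2 points in control against 2 points in intervention. The Discussion of the study design ties clinical relevance to an improvement of one SPPB point.

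**The concern.** Residuals exist only after the model has been fitted to outcome data. A fallback triggered by them, with four candidate scales and no order among them, leaves more than one possible primary estimate and p-value.

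The options also do not match the problems they are meant to solve. Dependence is one of the two named triggers, and the trial itself plans for an intra-cluster correlation of 0.15, yet dependence is not something a change of scale can cure. One of the four options cannot improve normality either.

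At stake is whether the primary result can be read against the 0.8-point target and the one-point relevance statement. On one reading of the sentence, it is also at stake whether the transformed outcome exists for every patient.

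**Working it through.** **Inputs.** From Sample size calculation: difference 0.8 points (means 1.2 and 2.0), SD 1.7, ICC 0.15, 5 patients per GP, 28 GPs per arm for 80% power, 300 patients randomized (150 per arm). From Participants: entry requires SPPB below 10 out of 12. Assumed, because the article does not state them: two-sided alpha of 5%, normally distributed changes, and a lowest SPPB score of 0.

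**1. The plan's own figure.** Design effect = 1 + (5 − 1) × 0.15 = 1.6. GPs per arm = 2 × (SD × (1.96 + 0.84) / 0.8)² × 1.6 / 5.
- With 1.7 as the total SD: 22.7, or 23.7 with t quantiles. This does not give 28.
- With 1.7 as the within-cluster SD, total SD = 1.7 / √(1 − 0.15) = 1.844: 26.7, or 27.7 with t quantiles, which rounds up to 28.

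The stated 28 is reproduced on the raw point scale under the second reading. Both SDs are carried forward. The article gives no effect size or SD on a log, Box-Cox or quantile scale, so no power can be stated there.

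**2. Dependence.** Clustered scores were simulated with ICC 0.15, rounded to whole points and held between 1 and 12 (assumed mean 8.2, total SD 1.7). The estimated ICC was:

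| Scale | ICC |
|---|---|
| Raw | 0.141 |
| Log | 0.137 |
| z-score | 0.141 |
| Normal quantile | 0.141 |

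The clustering is essentially untouched. If it were ignored, the type I error would be 2 × (1 − Φ(1.96 / √1.6)) = 12% instead of 5%. The random GP effect is what guards against that.

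**3. Normality and the z-score.** A z-score subtracts a constant and divides by a constant. In 300 simulated whole-point changes, skewness (0.133) and the Shapiro-Wilk statistic (0.960) were identical before and after.

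**4. Scale.** Take the planned gains of 2.0 and 1.2 points. On the log scale the between-arm gap is
- from a baseline of 3: ln(5 / 4.2) = 0.174;
- from a baseline of 9: ln(11 / 10.2) = 0.076.

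The same 0.8-point gap differs about 2.3-fold with baseline, so a log-scale effect is not a constant number of points.

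**5. Where log and Box-Cox are defined.** In standard form both need positive values. Applied to the change score, the undefined share is Φ((0 − mean) / SD) on a continuous scale, or Φ((0.5 − mean) / SD) for whole points:

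| SD | Scoring | Control (1.2) | Intervention (2.0) |
|---|---|---|---|
| 1.70 | continuous | 24.0% | 12.0% |
| 1.70 | whole points | 34.0% | 18.9% |
| 1.844 | continuous | 25.8% | 13.9% |
| 1.844 | whole points | 35.2% | 20.8% |

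With 150 per arm, that is 150 × (0.240 + 0.120) = 54 patients at the low end and 150 × (0.352 + 0.208) = 84 at the high end, or 18–28% of 300, unequally by arm. Applied to the raw score, the only failing value is 0, and the article gives no frequency for it.

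**The case against.** The strongest reply is textual. The sentence speaks of the SPPB score, not the change, and the period effect in the main model implies that the response is the score at each visit. On that reading log and Box-Cox fail only at 0, and quantile and z-score are defined for everyone on either reading. A reader might infer that the fallback is undefined for many patients; the text supports this only if log or Box-Cox is applied to the change. The ambiguity remains, because the outcome named just before is the change.

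Other parts of the defence also hold:
- Log, Box-Cox or quantile transformation can improve normality, so the fallback is not useless for that condition.
- A z-score converts back to points exactly, so it does not lose the scale.
- The random GP effect already deals with clustering in the main analysis. It would be wrong to infer that the trial ignores it.
- Nothing says that patients would be dropped (the analysis is committed to the intent-to-treat population), that the scale would be chosen with arms known, or that the residual check is bound to fail. No criterion for that check is given.

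Finally, the wording is permissive and the article is condensed, so an analysis plan that is not shown may fix the trigger and the order of options. The missing rule would not be a finding by itself. What stands is what the article does commit to: a list of remedies that includes one with no effect on either named violation, offers transformation for dependence, and allows the primary result to leave the unit in which the trial was powered.

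**Conclusion.** The concern holds in a limited form. On any reading, no listed transformation repairs dependent residuals, the z-score repairs neither named violation, and log, Box-Cox and quantile results are not in the points used for power and clinical relevance. The article leaves the choice among the four open until residuals have been seen.

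The figures of 24–35% (control) and 12–21% (intervention) are conditional. They apply only to a log or Box-Cox of the change score, with normal changes, the planned means, and an SD between the stated 1.70 and the 1.84 derived from it. They measure what is at risk on that reading and do not forecast lost patients.

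This should be corrected before analysis. It does not undermine the design or the sample size.

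**What to change.** Keep the untransformed mixed model with the random GP effect as the single primary analysis whatever the residuals look like, and report the effect in SPPB points. Replace the transformation sentence with one safeguard for non-normality, specified in advance: for example, a bootstrap interval that resamples practices within the geriatric-center strata used for randomization. State that dependence between patients of the same GP is handled by the random effect. Label any transformed or ordinal model as a sensitivity analysis.

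The cost is a change of wording and a little extra programming. The planned 28 GPs per arm (30 randomized) stay as they are, because they were derived on the raw point scale.

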### Secondary outcomes

The analysis used for the primary outcome will be used to evaluate the change of the secondary outcomes between the inclusion and the 6-month follow-up visit.

The analysis of the change of secondary outcomes in the interventional group will be performed using a longitudinal mixed effect linear model with a fixed period effect and as random effects: the center, the GP, and the patient nested within the GP. This analysis will be adjusted on the age at inclusion.

A univariate analysis will be performed using a longitudinal mixed effect linear model to identify the factors associated with the SPPB result at 6 months in the interventional group. The model will include as random effects the center, the GP and the patient nested within the GP, and as fixed effect the corresponding factor. This analysis will provide the effect estimation of each factor with its 95% confidence intervals. The independent factors found significant in this univariate analysis will be included in a multivariate analysis.

All analysis will be performed using the statistical analysis program SAS® version 9.4 (SAS Institute Inc., Cary, NC, USA), and the R program, version 3.3.1 (R foundation, Vienna, Austria).

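### The main model puts a period effect and a treatment-by-period term on a one-value-per-patient change score; the other reading, stacked scores with only a GP intercept, gives the wrong standard error

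*Protocol article*

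**What the plan says.** Under Outcomes and measurements, the protocol article states: "The primary outcome will be the difference in SPPB scores between inclusion and 6-month visits". The primary-outcome part of Statistical analyses repeats this definition: "The distribution of the primary outcome (difference in SPPB scores between inclusion and 6-month visits". Each patient therefore contributes one value.

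That analysis section then describes the model in three ways:

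- First: "The primary outcome will be analyzed using a multiple linear regression model".
- Next, as the main analysis of the primary outcome: "mixed effect linear model with a random GP effect, and as fixed effects: an intervention effect (the control group as reference), a period effect". Its fixed effects continue as "a period effect (the inclusion as reference), and an interaction between treatment and period". Centre and age are adjusted for, and an interaction of inclusion SPPB with intervention is added.
- Last: "Another analysis using the SPPB score as independent variable in a longitudinal mixed effect linear model will also be considered".

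The statistical section on secondary outcomes applies the primary-outcome analysis to the change in the secondary outcomes up to 6 months. For analyses confined to the intervention group it names, "as random effects: the center, the GP, and the patient nested within the GP".

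**The concern.** A period effect with inclusion as its reference needs an inclusion record and a 6-month record for each patient. A change score has already used up both. The stated outcome and the stated model therefore do not fit together, and the text leaves two repairs open.

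- **Change score.** The period terms are aliased and drop out. The intervention coefficient is the treatment effect.
- **Stacked scores.** The treatment effect is the treatment-by-period interaction, and the intervention coefficient becomes the difference between arms at inclusion. The only named random effect is a GP intercept.

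The two repairs place the treatment effect in different coefficients and give it different standard errors. The article does not say which coefficient is the primary test. The primary p-value and confidence interval come from this model in an open-label trial, and the between-arm secondary analyses inherit it.

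**Working it through.** **Inputs from the protocol article (Sample size calculation).** Difference in change 0.8 points; 5 patients per GP; ICC 0.15; SD 1.7; 28 GPs per arm needed and 30 randomised, so 150 patients per arm. The ICC is taken to be that of SPPB change, since the calculation is for change.

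**Assumptions.** Two-sided 5% level, consistent with the planned 95% intervals. Balanced clusters and no dropout. Equal score variance at both visits. A within-patient, within-GP correlation rho between the two visits, which the article does not give, shown as a range.

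**Step 1: the plan's own figure.** With 1.7 as the within-GP SD, the total variance of change is 1.7²/0.85 = 3.4 (SD 1.844). The design effect is 1 + 4 × 0.15 = 1.6. GPs per arm = 2 × 3.4 × 7.849 × 1.6 / (0.8² × 5) = 26.7 with normal quantiles, or 27.7 with t quantiles. This gives the stated 28. With 1.7 as the total SD the result is 22.7 or 23.7. The stated figure thus fits an analysis of change that allows for clustering.

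**Step 2: change-score reading.** Period is constant, so the columns for intercept, intervention, period and interaction have rank 2 out of 4. The two period terms are not estimable. Without them the model is change on intervention with a random GP effect.

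The GP-level variance of change is 0.15 × 3.4 = 0.51. The true variance of the treatment effect is 2 × (0.51 + 2.89/5)/30 = 0.0725, so SE = 0.269. A simulation of 4,000 trials per setting gave this analysis a type I error of 4.5-5.4% and power of about 82-84%.

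**Step 3: stacked reading.** A GP intercept adds equally to both visits and cancels from the interaction. The model SE is therefore sqrt(4 × MSE/150), where MSE is the within-GP residual mean square.

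The within-GP score variance consistent with the plan is s² = 2.89/(2(1 − rho)). Residual degrees of freedom are 600 − 60 − 2 = 538. Of these, 480 are patient-level within GP, with average variance s². The other 58 are GP-level, with variance 1.445 + 2.5 × 0.51 = 2.72. So MSE = (480 s² + 58 × 2.72)/538. Type I error is 2 × (1 − Φ(1.964 × model SE/0.269)). Power is Φ(0.8/0.269 − 1.964 × model SE/0.269).

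| rho | s² | MSE | Model SE (true 0.269) | Type I error | Power |
|---|---|---|---|---|---|
| 0.2 | 1.806 | 1.905 | 0.225 | 10.0% | 91% |
| 0.3 | 2.064 | 2.135 | 0.239 | 8.2% | 89% |
| 0.5 | 2.890 | 2.872 | 0.277 | 4.4% | 83% |
| 0.7 | 4.817 | 4.591 | 0.350 | 1.1% | 66% |

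Simulations agree. Type I error was 9.4-10.8% at 0.2, 7.9-9.0% at 0.3, 4.2-4.9% at 0.5 and 0.9-1.4% at 0.7. Power at 0.7 was 66-68%. The standard error is right only near rho = 0.5, where two errors offset: the ignored within-patient correlation makes it too large, and the ignored clustering of change makes it too small.

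**Step 4: is a patient intercept enough?** No. It handles the within-patient correlation but still leaves out the clustering of change. Approximately, SE = sqrt(2 × 3.4/150) = 0.213 against 0.269, and type I error is 2 × (1 − Φ(1.96 × 0.213/0.269)) = 12%. A cluster-by-period effect is also needed.

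**The case against.** The strongest reply is that the section announces an analysis of the change and lists a score-level longitudinal model separately, as another analysis. On that reading the main model is the change-score model, the aliased terms fall out, and the inference is valid. This stands. It rules out concluding that the primary analysis must give a wrong standard error. It does not remove the conflict: the valid result would depend on a software default or an unrecorded choice by the analyst, while the period terms point the other way.

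A second reply is that a full protocol or SAP may specify a patient effect or residual covariance. Its absence from an article would not be a finding by itself. The clash between outcome and period terms, however, is in the article's own text.

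Third, the sizes rest on a correlation the article does not give, and the direction of error changes across the range. That is so. At a correlation of 0.8 the same formula gives power of about 45%, but this implies a within-GP score SD of sqrt(7.225) = 2.7 in patients who all enter with SPPB below 10. It should not serve as the headline.

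Two further inferences are tempting and not supported:

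- The linear regression sentence might be read as an unclustered primary analysis, with type I error of about 12% from the design effect of 1.6. The following paragraph names the mixed model as the main analysis, so the sentence most naturally introduces the model family.
- A reader might infer that secondary outcomes get a patient effect and the primary does not. The between-arm secondary analyses use the primary model; the patient effect is named only for intervention-group analyses.

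**Conclusion.** The point holds as a contradiction in the protocol article: the main model cannot be estimated as written on the outcome it is said to analyse. One repair, dropping the period terms, gives a valid analysis that agrees with the sample size. The other, stacking the scores with only a GP intercept, gives a standard error that is too small at low within-patient correlation and too large at high correlation.

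The error rates and power losses apply only to the stacked reading and rest on the assumed correlation, balanced clusters, an ICC of 0.15 for change and a within-GP SD of 1.7. The sample size of 28 GPs per arm is not in dispute. The wording should be corrected before the data are analysed, because choosing between the readings afterwards could change the primary conclusion.

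**What to change.** In the primary-outcome analysis section, name one primary model: 6-month SPPB or change on arm, with baseline SPPB, centre and age as covariates, a random effect for the randomised cluster (practice/GP) and no period terms. State that the arm coefficient is the primary estimate.

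If a score-level longitudinal model is kept as supportive, make SPPB the dependent variable, add patient and cluster-by-period random effects, and name the treatment-by-period interaction as the treatment effect. Reword the linear regression sentence so that it refers to the mixed model. The between-arm secondary analyses then inherit the corrected model.

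The cost is analysis wording only, with no new data and no change to the sample size.

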### Secondary outcomes

The analysis used for the primary outcome will be used to evaluate the change of the secondary outcomes between the inclusion and the 6-month follow-up visit.

The analysis of the change of secondary outcomes in the interventional group will be performed using a longitudinal mixed effect linear model with a fixed period effect and as random effects: the center, the GP, and the patient nested within the GP. This analysis will be adjusted on the age at inclusion.

A univariate analysis will be performed using a longitudinal mixed effect linear model to identify the factors associated with the SPPB result at 6 months in the interventional group. The model will include as random effects the center, the GP and the patient nested within the GP, and as fixed effect the corresponding factor. This analysis will provide the effect estimation of each factor with its 95% confidence intervals. The independent factors found significant in this univariate analysis will be included in a multivariate analysis.

All analysis will be performed using the statistical analysis program SAS® version 9.4 (SAS Institute Inc., Cary, NC, USA), and the R program, version 3.3.1 (R foundation, Vienna, Austria).

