#### Secondary outcomes

The change of the secondary outcomes between the inclusion, 6, and 12-month follow-up will be analyzed. Secondary outcomes are: physical performance evaluated by the PASE [30] and sedentary behavior inspired by Gardiner et al. [31], and the distance walking; autonomy evaluated by the ADL and IADL [32]; quality of life evaluated by the SF-12 scale [33]; the number of serious injuries, hospitalizations, and institutionalizations, falls with healthcare consumption; nutritional status: weight, BMI, albuminemia (adjusted on CRP level) and MNA [34].

Additional outcomes will estimate prevalence of patients over 70 years of age with mobility limitation, adherence of patient and GPs to the program, and describe geriatric diagnosis after the consultation for the intervention group.

At baseline, GPs will collect data from the patients social environment EPICES score) comorbidities (Charlson index) [37], depression symptoms (GDS) [38], and medication inventory.

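### Every secondary outcome, event counts included, is assigned the linear model of 6-month change; as printed, Table 3 has no month-6 value for hospitalization or institutionalization

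*Protocol article*

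**What the plan says.** The list under Outcomes and measurements, Secondary outcomes, places "the number of serious injuries, hospitalizations, and institutionalizations, falls with healthcare consumption" beside continuous scores such as the PASE, the SF-12 and BMI. It promises results at both follow-up times: "The change of the secondary outcomes between the inclusion, 6, and 12-month follow-up will be analyzed".

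Under Statistical analyses, Secondary outcomes, one rule covers the comparison between groups: "The analysis used for the primary outcome will be used to evaluate the change of the secondary outcomes between the inclusion and the 6-month" assessment. The analysis it refers to is described under Statistical analyses, Primary outcome, as "using a mixed effect linear model with a random GP effect, and as fixed effects: an intervention effect (the control group as reference), a period" term and the treatment-by-period interaction. If the linear assumptions fail, the only fallback is "a transformation (logarithmic or even Box-Cox, quantile, or z-score) of the SPPB score will be considered".

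The other analysis given for these outcomes is confined to one arm and is also linear: "The analysis of the change of secondary outcomes in the interventional group will be performed using a longitudinal mixed effect linear model".

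The visits at which each outcome is collected are in Table 3 ("Schedule of outcome assessments").

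**The concern.** The rule makes no distinction by type of outcome. It sends sparse counts, and an event that most patients will have at most once, through a model built for a 12-point score. It also fixes the horizon at 6 months for outcomes that the schedule does not collect at 6 months.

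Two things are at stake. For hospitalization and institutionalization, the plan as written yields no comparison between arms. For falls it yields a comparison, but of a difference between a count from before inclusion and a count from after it, which is hard to interpret. The Background names falls and institutionalization among the consequences of mobility limitation, so these are not incidental outcomes.

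**Working it through.** **Step 1: schedule against rule.** The plan gives no figure for these outcomes, so the first check sets Table 3 beside the rule. An inclusion-to-6-month change needs a value at baseline and one at month 6. The marks below are the same in both arms.

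| Outcome | Baseline | M6 | M12 | 6-month change? |
|---|---|---|---|---|
| Hospitalization | yes | no | yes | no: M6 missing |
| Institutionalization | no | no | yes | no: both missing |
| Serious falls | yes | yes | yes | yes |
| Serious injuries | no row of its own | – | – | cannot be judged |

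In the primary model the effect on change is the treatment-by-period interaction. With a single record at month 12 and no baseline, that interaction cannot be estimated for institutionalization. For hospitalization it could be estimated only from baseline to month 12, and the rule does not state that comparison.

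**Step 2: horizon.** The outcome list promises change to 6 and 12 months. The only between-group rule stops at 6 months, and the other analysis covers the intervention arm alone. Hospitalization and institutionalization therefore have no stated between-group analysis at month 12.

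**Step 3: fit of a linear model to a count change.** The document gives no event rates, so these are assumptions: mean count λ per period, equal-length periods before and after inclusion, and patient-level gamma frailty with shape 0.5. Then

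- Var(follow-up count) = λ + 2λ²
- Var(change) = 2λ
- ratio = 2/(1 + 2λ)
- information lost against the follow-up count alone = 1 − (1 + 2λ)/2

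| λ | Ratio | Information lost | Change exactly 0 (simulated) | Excess kurtosis (simulated) |
|---|---|---|---|---|
| 0.05 | 1.82 | 45% | 92% | 15.7 |
| 0.1 | 1.67 | 40% | 86% | 10.9 |
| 0.3 | 1.25 | 20% | 72% | 7.6 |
| 0.5 | 1.00 | 0% | 65% | 7.1 |

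The simulated ratios were 1.83, 1.68, 1.25 and 1.00, in agreement with the formula. No monotone transformation removes a point mass of 65% to 92% at zero, so the stated fallback would not help even if it were extended beyond the SPPB.

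**Step 4: type I error.** The simulation used 60 GPs with 5 patients each (the planned 300), 3,000 repetitions per rate, and a t-test on GP means of the change. It rejected in 5.3%, 4.9%, 5.9% and 5.4% of repetitions for the four rates in order. It contained no between-GP variation and used GP means in place of the full mixed model, so it is indicative only.

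**Step 5: institutionalization as a proportion.** With 150 patients per arm, assumed risks of 2%, 5%, 10% and 20% give 150 × p = 3, 7.5, 15 and 30 events per arm. Skewness, (1 − 2p)/√(p(1 − p)), is 6.9, 4.1, 2.7 and 1.5.

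**The case against.** The strongest reply is that a journal article condenses the full protocol, and that the choice of model for each outcome usually belongs in the analysis plan. That would answer silence. Here the article states a rule for all secondary outcomes, and the rule conflicts with the article's own schedule.

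A second reply is that Table 3 itself looks condensed. SPPB appears twice, and the footnote defines CRP, GDS and EPICES, which have no rows under those names. If event dates were recorded at month 12, counts to month 6 could be derived. This stands as a limit: the finding is that the 6-month change cannot be formed from the schedule as printed. The document does not say that dates are collected. Taking every patient as not institutionalized at inclusion would supply a baseline but not a month-6 value.

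A third reply also stands. With 60 clusters, a difference in mean counts can be estimated and its type I error stays near nominal. A reader might infer that the falls analysis is invalid or prone to false positives; the simulation does not support that.

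A reader might also infer that exposure time is ignored. The article is silent on person-time and on the handling of death, and such details are commonly left to the analysis plan, so this is not part of the point.

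**Conclusion.** The rule as written cannot be carried out for hospitalization and institutionalization, and it leaves both without a stated comparison between arms at month 12. This rests only on the text and on Table 3 as printed.

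For falls, the linear model of change is misspecified, hard to interpret and may lose precision. The loss is 0% to 45% over the assumed rates, and it depends on event rates, on the correlation between periods and on the length of the baseline recall window, none of which the document gives. A single percentage should not be quoted, and none applies to the two outcomes with no 6-month change.

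It is tempting to say that exactly two of the four event outcomes lack month-6 data. That is not established, because serious injuries have no row in Table 3.

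The primary outcome and the sample size are unaffected. The same schedule mismatch reaches two nutritional outcomes: MNA is marked at baseline only, and albuminemia has no row.

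**What to change.** Keep the linear mixed model for continuous scores, and state a separate rule for events:

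- **Falls, serious injuries, hospitalizations:** analyse counts over follow-up with a count model, for example negative binomial or Poisson, adjusting for the baseline count where it is collected. Use a person-time offset where end-of-follow-up dates are available.
- **Institutionalization:** analyse the proportion by month 12, for example with a logistic or modified Poisson model.
- **Clustering:** include a GP or practice random effect, or use cluster-robust variance, in each model.
- **Horizon:** match Table 3, with month 12 for hospitalization and institutionalization, and months 6 and 12 for falls. State when serious injuries are recorded.

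The named models are examples. What is needed is a model suited to the type of outcome and a horizon at which data exist.

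The cost is small: a little more analysis work and different effect measures across the secondary outcomes. It may not be nil for data, since person-time needs dates of death or withdrawal, and a baseline injury count is not listed in Table 3. If a 6-month result for hospitalization or institutionalization is wanted, month-6 records or event dates must be added to the collection. No sample-size figure changes.
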